# Abstract

## Background

Excessive consumption of alcohol increases the risk of a range of diseases, including liver disease and many cancers. One promising intervention to reduce alcohol selection and consumption is increasing the availability of non-alcoholic drinks, relative to the proportion of alcoholic drinks, which has been shown to reduce alcohol selection in online settings. However, there is an absence of evidence concerning the impact of availability on alcohol purchasing. The aim of this study is to estimate the impact of altering the relative availability of a subset of drink options by increasing the proportion of non-alcoholic drinks and decreasing the proportion of alcoholic drinks, on online selection and purchasing of alcohol.

## Methods

*Study design:* Participants will be randomly assigned to one of three conditions in an experiment with a between-subjects factor of drink subset availability (i. 75% non-alcoholic, 25% alcoholic ii. 50% non-alcoholic, 50% alcoholic iii. 25% non-alcoholic, 75% alcoholic), in which the relative proportion presented (%) of alcohol-free beer, alcohol-free cider, alcohol-free wine and soft drinks will vary, compared to alcoholic beer, cider and wine options.

*Primary outcome*: number of alcohol units (i.e. the quantity of pure alcohol) selected (with intention to purchase).

*Procedure*: A sample of adults in England and Wales who consume alcohol (i.e., beer, cider and/or wine) at least weekly, and purchase these drinks at least monthly online at Tesco (minimum £20 monthly spend), will be recruited by a research agency (Roots Research). Participants will be directed to the drink selection task to choose drinks they would like to purchase as part of their next grocery shop. They will then be directed to complete their grocery shop via Tesco online, including the drinks previously selected as well as any other grocery items. They will be asked to confirm their delivery slot within 48 hours of the selection task and send proof of purchase (i.e., itemised receipt) within 48 hours of the delivery date and time.

## Study context

The results of this study will provide information about the impact of altering the relative availability of a subset of drink options, by increasing the presented proportion of non-alcoholic drinks and decreasing the proportion of alcoholic drinks, on the number of alcohol units selected and purchased online. The results will inform future field studies that aim to develop evidence regarding alcohol availability interventions.

Corresponding author: [name], [contact]

# Background

Excessive alcohol consumption is one of four modifiable behaviours, as well as tobacco use, physical inactivity and unhealthy diet, which are major contributors to non-communicable disease, such as cancer, heart disease and stroke (World Health Organisation, 2018). Traditional approaches to reducing alcohol consumption often involve providing information about harms linked to consumption. Interventions focused on information provision have limited population level effects and may serve to exacerbate health inequalities (Marteau, Hollands, & Fletcher, 2012). Given the known impact of environmental cues on consumption behaviours, an alternative approach is to alter the small-scale environments in which they occur (Hollands et al., 2017).

One promising intervention is increasing the availability of non-alcoholic drinks relative to the proportion of alcoholic drinks, which has been shown to reduce alcohol selection in online settings. According to the Typology of Interventions in Proximal Physical Micro‐Environments (TIPPME) (Hollands et al., 2017), this is classified as an *‘Availability x Product’* intervention. A recent conceptual framework of availability interventions described three possible categories of changes that could be implemented (R. Pechey, Hollands, Carter, & Marteau, 2020). An intervention may: i) alter the absolute availability of options (e.g., increase the total number of non-alcoholic and alcoholic drink items available without changing their relative proportions); ii) alter the relative availability of a subset of options (e.g., increase the proportion of non-alcoholic drinks relative to alcoholic drinks while keeping the overall number of drink items constant; thereby reducing the number of the latter); or iii) alter both the absolute and relative availability (e.g., increase the total number of non-alcoholic drinks, increasing their relative proportion to alcoholic drinks, as well as the total number of drink items).

Research has generally focused on interventions that alter relative availability only, as space restrictions often fix the total number of items within a selection (e.g., in vending machines or cafeterias). However*,* a recent online study found that increasing both the absolute and relative availability, or only the relative availability, of non-alcoholic compared to alcoholic drinks increased their selection (Blackwell et al., 2020). The proportion of participants choosing a non-alcoholic drink increased from 36% (range comprised two non-alcoholic and two alcoholic drinks) or 39% (range comprised four non-alcoholic and four alcoholic drinks) when equal proportions of drink types were available, to 49% when three-quarters of drinks available were non-alcoholic (range comprised six non-alcoholic and two alcoholic drinks). It is notable that there was no meaningful difference in non-alcoholic selection between the two conditions in which there were equal proportions of drink types (i.e., an increase in absolute availability only), which suggests that altering the relative availability (i.e., increasing the proportion of one subset thereby reducing another) may be particularly important for changing selection behaviour.

The current market for alcohol-free beer, alcohol-free wine and alcohol-free spirits is small but rapidly increasing (The Morning Advertiser, 2019). Interventions that increase the availability of these products have the potential to raise consumer awareness through greater exposure, widen consumer choice and the chances of identifying a preferred option, and shift social norms regarding their selection and consumption (R. Pechey et al., 2020). Similar interventions that have increased the proportion of healthier food products demonstrated increases in healthier food purchasing or consumption (Allan, Querstret, Banas, & de Bruin, 2017; Grech & Allman-Farinelli, 2015; Hollands et al., 2019; Rachel Pechey et al., 2019). However, the evidence base for availability interventions regarding alcohol products is small, and there is currently an absence of evidence for the impact on alcohol purchasing or consumption (Hollands et al., 2019).

The aim of this study is to estimate the impact of altering the relative availability of a subset of drink selection options, to increase the proportion of non-alcoholic drinks (alcohol-free beer, cider and wine and soft drinks) and decreasing the proportion of alcoholic drinks (beer, cider and wine) (i.e., decreasing the number of alcohol units within the range of available products), on the number of alcohol units that are i) selected and ii) purchased online.

# Study objective

The primary objective of this study is to estimate the impact on the amount of alcohol units of drinks selected by altering the relative availability of a subset of drink options, by increasing the proportion of non-alcoholic drinks (alcohol-free beer, cider and wine and soft drinks) and decreasing the proportion of alcoholic drinks (beer, cider and wine) presented.

For practical reasons, non-alcoholic drinks of interest will be restricted to products categorised as either alcohol-free beer (≤0.5%^[[1]](#footnote-1)^ alcohol by volume, ABV), alcohol-free cider (≤0.5% ABV), alcohol-free wine (≤0.5% ABV), or soft drinks that are not aimed at children (e.g., premium still or sparkling fruit flavoured drinks, or mixers such as tonic water, soda water or ginger ale). This definition aims to avoid including drinks purchased as part of the grocery shop that may not be considered as alternatives for alcohol or are primarily drinks for children (e.g., tea, coffee, squash, milk-based drinks, juice).

# Hypothesis

Altering the relative availability of a subset of drink options by increasing the proportion of non-alcoholic drinks (alcohol-free beer, cider and wine and soft drinks) and decreasing the proportion of alcoholic drinks (beer, cider and wine) will reduce the number of alcohol units selected.

# Methods

**Study design**

Participants will be randomly assigned to one of three conditions in an experiment with a between-subjects factor of drink subset availability (i. 75% non-alcoholic, 25% alcoholic ii. 50% non-alcoholic, 50% alcoholic iii. 25% non-alcoholic, 75% alcoholic), in which the relative proportion (%) of alcohol-free beer, cider and wine and soft drinks will vary, compared to alcoholic beer, cider and wine options.

## Study site

The studies will be conducted online, designed and hosted on the Qualtrics online survey platform (<http://www.qualtrics.com/>).

## Participants and recruitment

UK adults (N=600 recruited to achieve 510 completers) who consume alcohol (i.e., beer, cider and/or wine) at least weekly, and purchase these drinks at least monthly online from Tesco (minimum £20 monthly spend on these drinks), will be recruited to the study through a recruitment agency (Roots Research: <https://rootsresearch.co.uk/>).

Participants will be reimbursed £25 on study completion. Participants who begin the study but do not complete it will not be reimbursed, which will be explained at the start of the study.

### *Inclusion criteria*

1. Aged 18 years or over;
2. Current Tesco online customer;
3. Regularly consume alcohol – beer, cider and/or wine (i.e., at least once a week);
4. Regularly purchase alcohol – beer, cider and/or wine – online at Tesco (i.e., at least once a month, minimum £20 monthly spend on these drinks);
5. Willing to select drinks from 64 options, shown in an online task, to purchase in next online shop at Tesco;

*(Note: Options will include different brands of beer, cider, wine, alcohol-free beer, alcohol-free cider, alcohol-free wine and soft drinks available at Tesco; no additional drinks from these categories should be added to the Tesco shop)*

1. Willing to complete online shop at Tesco, book a delivery (or Click and Collect) slot, and send the details to the research team within 48 hours of the drink selection task;
2. Willing to send proof of purchase (i.e., itemised receipt) to the research team within 48 hours of delivery or collection date;
3. Have a Tesco delivery or collection address in England or Wales.

### *Sample size determination*

A previous online study compared the impact on drink selection of altering non-alcoholic vs alcoholic drink availability (Blackwell et al., 2020). The results showed that availability of non-alcoholic drink options affected drink selection (binary outcome of alcoholic drink selected, yes/no) in the online setting. The proportion of participants selecting an alcoholic drink decreased from 74% when non-alcoholic drink availability was low (25% of drink options), to 61% when availability was medium (50% of drink options), and 51% when availability was high (75% of drink options) (i.e., a difference of 13% and 10%, respectively, between adjacent groups). However, only a single drink was selected in this online study and there was no intention to purchase the selected drinks, or opportunity to do so. There is limited evidence available within the literature from which to estimate the effect of the intervention on selection behaviour of multiple drink options with the intention to purchase where the outcome is units of alcohol.

A maximum sample size of 600 is possible with available resources. Assuming a sample size of 600 is recruited and allowing for attrition of 15%, this would result in 510 participants (170/group) in the analysis dataset. Based on the primary outcome of the amount of alcoholic units selected, for a two group t-test with alpha of 5% and power 80% an effect size of 0.3 could be detected. Using data from the test run (~5/group) the conservative estimate of the SD is 12.1 (i.e. the maximum group variance observed). This suggests a difference of at least 3.7 units alcohol selected between groups may be detected by a linear regression model.

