## Secondary outcomes

The above analysis will be repeated for most of the secondary outcomes. For the proportion of total drinks selected and purchased that are alcoholic we will use a binary logistic model based on the counts of drinks.

Each pairwise effect will be reported as a difference in means with 95% confidence interval (CI) of the mean, t statistics and p-values. For these pairwise comparisons only, a significant p value of 5%/3 will be adopted due to multiple comparisons. An umbrella p value and F statistic, between all three study arms, will also be reported.

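### The stated 80% power for 3.7 units assumes alpha 5%, but pairwise differences are judged at 5%/3; if that covers the primary outcome, power is about 66%

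*Protocol*

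**What the plan says.** **Sample size determination.** The section is explicitly about the primary outcome, alcohol units selected. Recruitment is capped by resources at 600. With 15% attrition, "this would result in 510 participants (170/group) in the analysis dataset". It then says that "for a two group t-test with alpha of 5% and power 80% an effect size of 0.3 could be detected". From the test run, "the conservative estimate of the SD is 12.1", and the section concludes: "This suggests a difference of at least 3.7 units alcohol selected between groups may be detected by a linear regression model". It makes no allowance for multiple comparisons.

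**Primary outcome: Selection.** A generalised linear model compares the three arms, with the 25% non-alcoholic arm as reference. The section gives no significance level and no rule for pairwise comparisons.

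**Secondary outcomes.** The primary analysis is to be repeated for most secondary outcomes. Pairwise effects are to be reported as differences in means with 95% confidence intervals, t statistics and p-values. Then: "For these pairwise comparisons only, a significant p value of 5%/3 will be adopted due to multiple comparisons". An F test across the three arms is also to be reported, without a stated alpha and without being described as a gate.

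**The concern.** A two-group t-test between arms is a pairwise comparison. The protocol works out the detectable difference for that comparison at one significance level and sets out to judge pairwise comparisons at a stricter one. If the stricter level applies to the primary outcome, the stated power belongs to a test that will not be run.

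Because recruitment is fixed by resources, the detectable difference is the main conclusion of the sample size section. It tells a reader how sensitive the trial is on its primary outcome, so it should match the criterion used there.

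**Working it through.** **Inputs from the protocol.** n = 170 per group; SD = 12.1 units; difference = 3.7 units; power 80%; alpha 5% in Sample size determination; pairwise threshold 5%/3 = 0.01667 in Secondary outcomes.

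**Assumption.** The protocol does not say whether the test is one- or two-sided. Two-sided is assumed because it reproduces the stated figure. A one-sided 5% test would give 88% power for 3.7 units.

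**Formulas (normal approximation).**
- Detectable difference = (z for 1 − alpha/2 + z for power) × SD × √(2/n)
- Power = Φ(difference / (SD × √(2/n)) − z for 1 − alpha/2)
- √(2/170) = 0.1085, so the standard error of a difference is 12.1 × 0.1085 = 1.312 units.

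**Step 1: reproduce the stated figure at alpha 5%.**
- (1.960 + 0.842) × 0.1085 = 0.304 SD; × 12.1 = 3.68 units. The non-central t gives 0.305 SD, or 3.69 units. Both round to the protocol's 3.7.
- Power for 3.7 units: 3.7 / 1.312 = 2.819; Φ(2.819 − 1.960) = Φ(0.859) = 80.5% (80.3% by t).

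The method is therefore identified, and only alpha is in question.

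**Step 2: the same calculation at alpha 5%/3.** The critical value rises from 1.960 to 2.394.
- Power for 3.7 units: Φ(2.819 − 2.394) = Φ(0.425) = 66.5% (66.0% by t; 66.2% with the 507 residual degrees of freedom of a three-arm model).
- Power for an effect size of exactly 0.30: 64.5% (64.1% by t).
- Detectable difference at 80% power: (2.394 + 0.842) × 0.1085 = 0.351 SD; × 12.1 = 4.25 units (0.352 SD, or 4.26 units, by t).

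**Step 3: how far this depends on the inputs.**

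| Setting (t-test, SD 12.1) | Power for 3.7 units | Detectable at 80% power |
| --- | --- | --- |
| 170/group, alpha 5% | 80.3% | 3.69 units |
| 170/group, alpha 5%/2 | 71.5% | 4.06 units |
| 170/group, alpha 5%/3 | 66.0% | 4.26 units |
| 200/group (no attrition), alpha 5%/3 | 74.3% | 3.93 units |

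The 5%/2 row would apply if only the two contrasts with the reference arm were tested; the protocol says 5%/3. Keeping 80% power for 3.7 units at 5%/3 would need 224 to 226 per group. With 15% attrition that is 3 × 224 / 0.85 = 791 to 3 × 226 / 0.85 = 798 recruited, above the cap of 600.

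**Step 4: what the 66% does not describe.** The umbrella F test is a different test. If it is run at 5% (an assumption) and the largest difference is 3.7 units, its power is about 71% with the middle arm midway and about 84% with two arms equal.

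**The case against.** **Placement.** The strongest objection is that the 5%/3 sentence stands under Secondary outcomes and is expressly limited in scope. Read literally, it leaves the primary pairwise tests at 5%, and the 80% is then right. This stands to the extent that the 66% has to be stated conditionally. Three features make the wider reading the more natural one:
- That paragraph is the only place that says how pairwise differences are reported and judged.
- The secondary analyses are described as a repeat of the primary one.
- The limiting word most readily separates pairwise tests from the umbrella test in the next sentence.

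**Family-wise error.** A reader might infer that the literal reading is faulty in any case, because three unadjusted 5% tests carry a family-wise error of about 12%. The protocol does not establish that. The figure assumes three ungated tests. Two ungated tests against the reference arm give about 9%. If the F test gated the pairwise tests, family-wise error under no difference between arms would stay at 5%. The protocol neither makes the F test a gate nor rules it out.

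**Null results.** A reader might also infer that a non-significant result would be taken to exclude 3.7 units. Nothing in the protocol says so, and the planned 95% confidence intervals will show what is excluded.

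**Size.** The shift from 3.7 to 4.3 units is small beside the uncertainty in an SD taken from about five people per group. With 4 degrees of freedom, a 95% interval around 12.1 is roughly 7 to 35, before allowing for the largest value having been chosen. That is true, but it does not justify calculating power at an alpha other than the one used.

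**Conclusion.** Wrong as written, on the natural reading of the protocol. The 3.7-unit figure is correct arithmetic at two-sided 5%, but the only pairwise threshold the protocol sets is 5%/3. If that threshold covers the primary outcome, power for 3.7 units is about 66% per pairwise comparison. The difference detectable with 80% power is then about 4.3 units (0.35 SD), roughly 0.6 units or 16% larger than stated. This rests on 170 analysed per group, an SD of 12.1 and a two-sided test.

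A reader might go further and conclude that the trial simply has 66% power, or that it must recruit more. The protocol supports neither. The first depends on where the 5%/3 rule applies, which the section heading leaves open. As for the second, the sample size was set by resources, and the protocol does not present 3.7 units as a minimum important difference that has to be met. The fault lies in the stated sensitivity, not in the design.

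**What to change.** 1. In Primary outcome: Selection, state that pairwise comparisons between arms are judged at 5%/3.
2. In Sample size determination, restate the result as: 170 per group, pairwise two-sided alpha 5%/3, 80% power for 0.35 SD, that is 4.3 units if the SD is 12.1.
3. If the sponsor instead intends 5% for the primary pairwise tests, keep 3.7 units, say so in the primary section, and say how multiplicity is controlled, for example by making the umbrella F test a gate.

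The change is to wording only. The number recruited, the model and the data collected stay as they are. Under steps 1 and 2, the only cost is a slightly less favourable stated figure.

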### *Withdrawal of participants*

Participants will be informed at the start of the study that they are free to withdraw at any time, by closing their web browser before submitting their responses in the online selection task, or not sending subsequent proof of purchase to the study team. Participants will only be reimbursed after the research team receive proof of purchase. If this is not received within seven days of the given delivery or collection date (following two email reminders), the research team will assume that the participant has withdrawn, and they will not be reimbursed. Participants will be made aware of these details in the information sheet before consenting to take part in the study.

## Randomisation

The study will be delivered on the Qualtrics platform, which will use an algorithm to randomise participants into one of the three conditions.

# Intervention

## Availability of non-alcoholic and alcoholic drinks

Participants will view: i. a range of beers, ciders and soft drinks, and ii. a range of wines and soft drinks. These two drink ranges will each show 32 drink options (Table 1). The full list of possible drinks displayed across conditions can be found in Appendix A. The order in which the two drink ranges (beer, cider and soft drinks first or wine and soft drinks first) are presented will be randomised. In each range, the drink options within the three sub-categories (i.e., i. beer and cider, alcohol-free beer and alcohol-free cider, or soft drinks, ii. wine, alcohol-free wine, or soft drinks) will be presented together under their respective headings but their order of presentation will be randomised. The relative availability (proportion) of non-alcoholic (alcohol-free beer, cider or wine alternatives and soft drinks) and alcoholic (beer, cider or wine) drink options – and therefore alcohol units – will vary according to the three conditions. Alcohol-free beer, cider and wine will be clearly labelled to ensure that they are not confused with alcoholic drinks. Each drink option presented will be a different brand, i.e., as the relative availability of non-alcoholic drink options increases, there will be a larger choice of brands from which to choose. Drink images will all be shown as bottles or cans, either as single items or multipacks, depending on the availability of products at Tesco. Participants will be able to select as many drinks as they would like to purchase in their household grocery shop.

# Measures

**Primary outcome measure**

- Number of alcohol units selected (with an intention to purchase). *Participants will be aware that they will be required to purchase the drink items chosen in the selection task and send proof of this to the research team. Therefore, the primary outcome of selection will be made in the context of intention to purchase and provide evidence of this behaviour.*

Units of alcohol – a measure of pure alcohol in a drink with one unit being 10ml or 8g of pure alcohol - will be calculated for all drinks that are >0% ABV (i.e. alcoholic and alcohol-free drinks).

